## Laboratory Procedures and Evaluations

HEMATOLOGY

Only as clinically indicated per institutional standard of care.

COMPREHENSIVE METABOLIC PANEL

Only as clinically indicated per institutional standard of care.

COAGULATION PANEL

Only as clinically indicated per institutional standard of care.

PREGNANCY TEST

A serum or urine pregnancy test is required during screening for all persons of childbearing potential. The pregnancy test is required within 7 days prior to study intervention and results must be available prior to administration of study agent. If the urine pregnancy test is positive, a serum pregnancy test must be performed per institutional standards.

AMYLASE ASSAY

Amylase levels will be drawn from all surgical drains, when present, on postoperative day 3 or 4±4, per standard of care prior following pancreas resections. In patients undergoing percutaneous drainage of a postoperative intra-abdominal fluid collection, amylase levels on the drained fluid will be drawn to evaluate for fistula. An amylase level >3 times the upper limit of normal from a surgical drain is sufficient for diagnosis of leak. Serum amylase will also be collected on the day drain amylase is collected as a referent.

## Biomarker, Correlative, and Special Studies

N/A

## Screening Assessments

A screening (consultation) visit may occur as part of standard of care. If a participant is eligible for the study after review of key inclusion/exclusion criteria, additional screening visits will be scheduled while staff members are requesting insurance authorization to participate in a clinical trial.

The following will be reviewed at screening visit:

• Clinical history and physical exam (per standard of care)

• Informed consent obtained and documented

Toxicities which occur prior to the start of treatment will not be subject to analysis. Consent must be obtained before initiation of any clinical screening procedure that are performed solely for the purpose of determining eligibility for this research study. Evaluations performed as part of routine care before informed consent can be utilized as screening evaluations if done within the defined time period.

## Baseline Assessments

Baseline screening evaluations are to be conducted within 4 weeks prior to start of protocol treatment. Imaging must be done within 4 weeks prior to start of protocol treatment.

## Early Termination or End of Treatment Visit

Any participant who undergoes early termination will undergo end of study visits depending on their progress in the protocol. Participants who have not received ICG injection are not considered enrolled, will not require a follow up visit and will be treated per standard of care. Participants undergoing termination following pancreatectomy will have an end of study visit at the time of their regular post-op visit and will be cared for per the standard of care.

## Follow-up

Per standard of care, participants will be followed by their attending surgeon and team postoperatively. Study follow-up will include acquisition of NSQIP outcomes, collected for the 30 days following pancreas resection for efficacy and safety of ICG. A follow-up visit will occur 14 days (± 7 days)-following hospital discharge, consistent with standard of care practices. Additionally, all subjects will be contacted by phone by a NSQIP nurse reviewer for approximately 30 days following the operation to collect standard NSQIP data, which is outside of the scope of this protocol.

## Unscheduled Visits

Unscheduled study visits may occur at any time if medically warranted. Any assessments performed (e.g., laboratory or clinical assessments) at those visits that, in the opinion of the investigator, are deemed related to this study should be recorded in the CRF.

## Schedule of Events

| Table X. Schedule of Procedures and Evaluations | | | | | | |
| --- | --- | --- | --- | --- | --- | --- |
| **Visit Days (± 3 Days)** | **Screening** | **Surgery** | **Postop day 3** | **Discharge day** | **Postop day 30** | **Follow-Up** |
|  | **Days**  **-28 to -1** | **Day 1** | **Day 4±3** | **Day +-14** | **Day 14-30** | **0-30 Days post surgery** |
| Informed consent | X |  |  |  |  |  |
| Inclusion/exclusion criteria | X |  |  |  |  |  |
| Medical history (including weight loss history within the last 6 months) | X |  |  |  |  |  |
| Prior/concomitant medications | X | X |  | X |  |  |
| Height and weight | X | X |  | X | X |  |
| Comprehensive physical examination | X |  |  |  |  |  |
| Physical Examination | X | X |  | X | X | X |
| Vital signs | X | X | X | X | X |  |
| ECG (if indicated) | X | X |  |  |  |  |
| Pregnancy test (if indicated) | X | X |  |  |  |  |
| Routine blood draw (1 tablespoon) |  | X | X |  |  |  |
| Review any adverse events |  | X |  |  |  |  |
| Review all medications |  | X |  |  |  |  |
| ICG |  | X |  |  |  |  |
| Pancreas resection |  | X |  |  |  |  |
| Follow-up data collection |  |  |  |  |  | X |
| Amylase from drain fluid |  |  | X |  |  |  |
| ***FOOTNOTES:*** | | | | | | |

# EFFICACY MEASURES

Diagnostic efficacy will be evaluated in this study by the presence of any leaks and its relation with intraoperative tissue data.

## Definition of Efficacy Measures

Signs of postoperative fistula

Amylase level 3x the upper limit of normal from drain fluid.

## Disease Evaluation

Evaluation for fistula formation is done via amylase fluid analysis on postoperative drain and clinical suspicion of its classical symptoms.

## ISGPS DEFINITION AND GRADING OF POSTOPERATIVE PANCREATIC FISTULA

We will grade each patient’s postoperative characteristics via the ISGPS grading system. Bile Leak (previously grade A): increased drain amylase activity > 3 times the upper limit of institutional normal serum amylase activity. Grade B: bile leak criteria plus any of the following: persisting peripancreatic drainage >3 weeks, clinically relevant change in management of POPF, POPF percutaneous or endoscopic specific interventions for collections, angiographic procedures for POPF related bleeding. Grade C: whenever Grade B fistula requires reoperation, has signs of infection related to POPF with organ failure, POPF related organ failure or POPF related death.^28^

# SAFETY

## Specification Of Safety Parameters

The Investigator is responsible for monitoring the safety of participants who have enrolled in the study. Safety assessments will be based on medical review of adverse events and the results of safety evaluations at specified time points as described in Section 8.10, Schedule of Events. Any clinically significant adverse events persisting at the end of treatment visit will be followed by the Investigator until resolution/stabilization or death, whichever comes first.

## Definitions

- - 1. Adverse Event (AE)

An adverse event is defined as any undesirable physical, psychological or behavioral effect experienced by a participant during their participation in an investigational study, in conjunction with the use of the investigational product, whether considered intervention-related (21 CFR 312.32 (a)). In general, this includes signs or symptoms experienced by the participant from the time of signing the informed consent to completion of the study.

AEs may include, but are not limited to:

- Subjective or objective symptoms spontaneously offered by the participant and/or observed by the Investigator or medical staff.
- Clinically significant laboratory abnormalities.
- A significant worsening of the participant’s condition from study entry.
- Disease signs and symptoms and/or laboratory abnormalities existing prior to the use of the study treatment that resolve but then recur after treatment.
- Disease signs and symptoms and/or laboratory abnormalities existing prior to the use of the study treatment which increase in frequency, intensity, or a change in quality after treatment.
  - 1. Serious Adverse Event (SAE)

An AE or suspected adverse reaction is considered "serious" if, in the view of either the Investigator or Sponsor-Investigator, it results in any of the following outcomes:

- Death,
- A life-threatening adverse event,
- In-patient hospitalization or prolongation of existing hospitalization,
- A persistent or significant incapacity or substantial disruption of the ability to conduct normal life functions, or
- A congenital anomaly/birth defect.
- GI bleeding or perforation requiring hospitalization
- Any procedure-related complications resulting in delay of adequate and timely discharge of hospital
  - 1. Unanticipated Problems (UP)

The Office for Human Research Protections (OHRP) considers UPs involving risks to participants or others to include, in general, any incident, experience, or outcome that meets all of the following criteria:

1. Unexpected in terms of nature, severity, or frequency given (a) the research procedures that are described in the protocol-related documents, such as the IRB-approved research protocol and informed consent document; and (b) the characteristics of the participant population being studied;
2. Related or possibly related to participation in the research (“possibly related” means there is a reasonable possibility that the incident, experience, or outcome may have been caused by the procedures involved in the research); and
3. Suggests that the research places participants or others at a greater risk of harm (including physical, psychological, economic, or social harm) than previously known or recognized.

This study will use the OHRP definition of UP.

- - 1. Severity of Event

The Investigator will grade the severity of each AE using, when applicable, the current version of the [CTCAE v5.0](https://safetyprofiler-ctep.nci.nih.gov/CTC/CTC.aspx). In the event of an AE for which no grading scale exists, the Investigator will classify the AE as defined below:

| **Grade 1:** | Mild; asymptomatic or mild symptoms; clinical or diagnostic observations only; intervention not indicated. |
| --- | --- |
| **Grade 2:** | Moderate; minimal, local or noninvasive intervention indicated; limiting age-appropriate instrumental ADL |
| **Grade 3:** | Severe or medically significant but not immediately life-threatening; hospitalization or prolongation of hospitalization indicated; disabling; limiting self-care ADL. |
| **Grade 4:** | Life-threatening consequences; urgent intervention indicated. |
| **Grade 5:** | Death related to AE. |
| *Note: a semi-colon indicates ‘or’ within the description of the grade.* | |

- - 1. Assessment of Causality Relationship To Study intervention

For all collected AEs, the clinician who examines and evaluates the participant will determine the AE’s causality based on temporal relationship and his/her clinical judgment. The degree of certainty about causality will be graded using the categories below:

| **Definitely Related:** | There is clear evidence to suggest a causal relationship, and other possible contributing factors can be ruled out. |
| --- | --- |
| **Possibly Related:** | There is some evidence to suggest a causal relationship. |
| **Unrelated:** | The AE is completely independent of study intervention administration, and/or evidence exists that the event is definitely related to another etiology. |

## Expectedness

The Investigator will be responsible for determining whether an AE is expected or unexpected. An AE will be considered unexpected if the nature, severity, or frequency of the event is not consistent with the risk information previously described for the study agent.

## Adverse Event List(s)

- - 1. Adverse Event List for ICG INJECTION

Detailed information about the risks and expected AE of ICG may be found in the current edition of the manufacturer’s information brochure. In brief, the most frequent adverse reactions were allergic reactions with nausea or hypotension. For more detailed information refer to 1.4.1.

## Time Period And Frequency For Event Assessment And Follow-Up

The occurrence of an UP, AE or SAE may come to the attention of study personnel during study visits and interviews of a study participant presenting for medical care, upon review by a study monitor, or during an audit. All AEs grade 3 or higher but not meeting the criteria for SAEs will be captured on the appropriate CRF. AEs of grade 1 and 2 will not be captured due to the well-characterized side effect profile of ICG for other indications, including IV ICG injection which is FDA approved. Information to be collected includes event description, time of onset, clinician’s assessment of severity, seriousness, expectedness, relationship to study product (assessed only by those with the training and authority to make a diagnosis), and date of resolution/stabilization of the event. All AEs grade 3 or higher occurring while on study must be documented appropriately regardless of relationship. All AEs will be followed to adequate resolution.

Any medical condition that is present at the time that the participant is screened will be considered as baseline and not reported as an AE. However, if the study participant’s condition deteriorates at any time during the study, it will be recorded as an AE after treatment with study intervention begins.

Changes in the severity of an AE will be documented to allow an assessment of the duration of the event at each level of severity to be performed. AEs characterized as intermittent require documentation of onset and duration of each episode.

At each study visit, the Investigator will inquire about the occurrence of AE/SAEs since the last visit. Events will be followed for outcome information until resolution or stabilization.

The Investigator will record all reportable events with start dates occurring after treatment with study intervention begins for 30 days after date of surgery. AEs will be evaluated using the current version of the [CTCAE v5.0](https://safetyprofiler-ctep.nci.nih.gov/CTC/CTC.aspx). At each study visit, the investigator will inquire about the occurrence of AE/SAEs since the last visit. Events will be followed for outcome information until resolution or stabilization. Any SAE that occurs after treatment with alternative therapy will be reported only if the Investigator or current treating physician has assessed the SAE as related to the study treatment.

## Reporting Procedures

- - 1. OHSU IRB Reporting of Unanticipated Problems and Adverse Events

Unanticipated Problems and AEs will be reported to OHSU IRB according to the policies, procedures and guidelines posted on the [OHSU IRB web site](http://www.ohsu.edu/xd/about/services/integrity/policies/all-irb-documents.cfm).

Events that must be reported by the Investigator to the IRB are detailed in the OHSU IRB **Investigator Guidance: Prompt Reporting Requirements (HRP-801)**. Events that meet the criteria for OHSU RNI must be reported to the IRB within 5 days of learning of the event. At a minimum, events requiring reporting to the IRB include:

- Any new or increased risk related to the research, including AEs or IND safety reports that require a change to the protocol or consent,
- New FDA black box warning,
- Publications identifying new risks,
- Data Safety Monitoring Board/Committee letters recommending changes or discussing new risks
- Unanticipated adverse device effect
- Unauthorized disclosure of confidential participant information
  - 1. Central Reporting of Adverse Events for Multi-Site Studies

A sub-site must notify the OHSU Coordinating Center of any SAE by phone, fax, or email no later than 24 hours after learning of the event. The sub-site must also report each event to the institution’s local IRB or other oversight entity per institutional policies/requirements. The sub-site will send the Coordinating Center supporting materials regarding the SAE, as well as [describe what sub-site must submit to coordinating center, for example: Knight SAE form, MedWatch form 3500, and/or any other trial specific reporting form (AESI, AECI)].

The Coordinating Center will review and submit SAE information to the FDA, OHSU IRB, sub-sites, and any other entities as required by federal and local policies/regulations, and any other applicable requirements.

The Coordinating Center is responsible for distributing IND and/or IDE Action Letters and/or Safety Reports, as applicable, to sub-sites for review and submission to their institution’s local IRB as required per site policy.

- - 1. FDA Reporting

Some events must be reported to the FDA through the MedWatch Voluntary reporting program, even if the trial involves a commercially available agent. Events to be reported include any UPs (i.e., not listed in the package insert) and any SAEs with a suspected association to the study intervention.

For studies conducted under an IND/IDE, the OHSU Coordinating Center Investigator is required to report certain events to the FDA per applicable regulations.

For multi-site investigator-initiated trials, the OHSU PI is the study sponsor and the following reporting responsibilities and requirements apply.

The sub-site investigator is required to report AEs to the Coordinating Center using a MedWatch report form and/or any trial-specific report form and supporting materials. Adverse events to be reported include any UPs (i.e., not listed in the package insert and/or IB) and any SAEs with a suspected association to the investigational product. The Coordinating Center will centrally assess all reported events and report any events to the FDA as warranted using the MedWatch 3500A Mandatory report form.

- - 1. Suspected Unexpected Adverse Reactions (SUSARs)

Per regulatory requirements, if an event is assessed by the Sponsor Institution as a Serious Unexpected Adverse Reaction (SUSAR), it is the responsibility of the Sponsor Institution to submit the SUSAR to Regulatory Authorities according to applicable regulations. In addition, the SUSAR will be distributed to the Investigators/sites utilizing a Council for International Organizations of Medical Sciences (CIOMS) report form, or the MedWatch 3500A form). The Investigator/site will submit a copy of the report to their respective IRB or IEC per the governing institutional requirements and in compliance with local laws and guidelines.

- - 1. Reporting Of Pregnancy

To ensure participant safety, each pregnancy or suspected pregnancy in a participant during study participation must be reported within 24 hours of learning of its occurrence. The sub-site investigator is required to notify the OHSU Coordinating Center by phone, fax, or email no later than 24 hours of learning of a pregnancy. The sub-site must also report each event to the institution’s local IRB or other oversight entity per institutional policies/requirements. The Coordinating Center will centrally assess the event and report to the manufacturer and any other entity as warranted. The sub-site will send the Coordinating Center information regarding the pregnancy using secure institutional email. Describe what sub-site must submit to Coordinating Center, for example: Knight SAE form template, MedWatch form 3500, and/or any other trial specific reporting form.

The investigator must follow the pregnancy to determine outcome, including spontaneous or voluntary termination, details of the birth, and the presence or absence of any birth defects, congenital abnormalities, or any pregnancy- or childbirth-related and/or newborn complications. The sub-site must report the outcome of the pregnancy to the Coordinating Center as defined above.

If participant becomes pregnant during the study, a separate consent form will be requested and will be submitted via modification. If during study participation a participant’s sexual partner becomes pregnant, the pregnancy and pregnancy outcomes must also be reported as described above. A separate consent form to report information regarding the pregnancy should be obtained from the pregnant individual.

## Study Stopping Rules

The overall study will be paused, and appropriate authorities (e.g., IRB, Knight Data and Safety Monitoring Committee) notified if the following events occur:

• Life-threatening grade 4 toxicity attributable to protocol therapy that is unmanageable, or unexpected.

• Death suspected to be related to ICG injection.

• As indicated by statistical stopping rules in this protocol.

# STATISTICAL CONSIDERATIONS

## Statistical Hypothesis

This is an open label, one arm phase II study to assess the diagnostic perfusion characteristics by intraoperative ICG injection on pancreatic leak rates. It is hypothesized that remnant pancreatic gland perfusion will be readily and objectively evaluated and that hypoperfusion will be associated with increased rates of pancreatic leaks postoperatively.

## Sample Size Determination

This primary objective of study is to detect the difference in leak rates between normal and reduced ICG perfusion group. Since there are no existing data of ICG perfusion in the pancreas, the sample size calculation was not based on the hypothesis but we provided the detectable difference between two groups. Anticipating the balanced number between two groups, our sample size of 50 will have 80% power to detect at least 25% difference in leaks rate between two group assuming 20% leak rate for normal ICG perfusion group.

We consider a liberal exclusion of 30% due to multiple and complex postoperative factors known to be associated with leaks. We anticipate screening 75 patients and enrolling 50.

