| **Statistical Analyses** | Chi-square test will be used to evaluate the association between leaks and perfusion. Logistic regression analysis will be further utilized to evaluate covariates influencing the presence/absence of leaks, with specific attention to the predictive value of percent maximum perfusion metrics and time to maximum metrics at the set timepoints in the protocol. With leaks of any severity occurring in a minimum 20% of pancreatectomies based on extensive published data. Our projected sample size of 50 will achieve 80% power to detect at least 25% difference in leaks rate between two group assuming 20% leak rate for normal ICG perfusion group.  We plan to enroll patients on a rolling basis. With a liberal estimated exclusion of 30% due to the multiple and complex postoperative factors known to be associated with leak (hemorrhage, sustained hypotension, vasopressor requirements included in “Exclusion Criteria”) we anticipate screening 75 patients and enrolling 50. The overall study will be paused if the following events occur: Life-threatening grade 4 toxicity attributable to protocol therapy that is unmanageable, or unexpected, death suspected to be related to ICG injection, as indicated by statistical stopping rules in this protocol. |

SCHEMATIC OF STUDY DESIGN

[figure not shown]

|  | **Preop visit** | **Surgery and Postoperative Period** | | | | |
| --- | --- | --- | --- | --- | --- | --- |
| **Procedure** |  | **Day 1 (Day of Surgery)** | **Day 4±3**  **(Post-operative Day 3)** | **Day of Discharge** | **Discharge + 7-14 Days (Post-Operative Follow-up)** | **Day 30** |
| Physical exam | x | X | X | X | X |  |
| Vital signs^1^ | x | X | X | X | X |  |
| ECG (if indicated) | x | X |  |  |  |  |
| Routine blood draw^2^  (1 tablespoon) |  | X | X |  |  |  |
| Drain Fluid Analysis for amylase |  |  | X |  |  |  |
| Pregnancy test (if indicated) | x | X |  |  |  |  |
| Review any adverse events |  | X |  |  | X | X |
| Review all other medications |  | X |  |  |  |  |
| ICG |  | X |  |  |  |  |
| Pancreas Resection |  | X |  |  |  |  |

TABLE OF CONTENTS

[TABLE OF CONTENTS 7](#_Toc1924134513)

[LIST OF TABLES 7](#_Toc453567276)

[LIST OF FIGURES 7](#_Toc1478094859)

[LIST OF ABBREVIATIONS 7](#_Toc1089401493)

[0. BACKGROUND INFORMATION AND SCIENTIFIC RATIONALE 9](#_Toc2112760570)

[0.0 Background 9](#_Toc1747993032)

[0.0.0 Overview of study disease(s) 9](#_Toc2072564894)

[0.0.1 Overview study intervention(s) 10](#_Toc2069882099)

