# STUDY DESIGN

## Description of the Study Design

*Refer to* Section 11*, Statistical Analysis for additional information regarding statistical methods used in this study.*

This is a Phase II study to assess diagnostic parameters of hypoperfused pancreatic cut edge via ICG and its relation to fistula formation versus conventional measurements. The study design consists of a single arm intervention group (n=50).

The trial will commence with the enrollment of the fifteen patients, after these 15 casesa logistics run-in of the OR ICG technique and timing will be done. During the logistics run-in, the PI will evaluate team satisfaction and measurement outcomes. This will be done through the application of a 3-question paper-based quality survey, attached in the supporting documents for the protocol. If an average score below 50% is given, study will be terminated to avoid negative impact on the logistics of pancreatectomies. Survey scores are calculated depending on the answer given, A= 0% B = 16.5% C = 33%. Minimum score 0 maximum score 100. Progressive study enrollment will continue throughout the adjustments, and enrollment will be halted if any major concerns arise. If the interim analysis does not result in study termination, enrollment of the remaining participants will resume to enroll a total of 50 patients completing study intervention and follow-up.

Aside from interim analysis evaluating logistics. A patient safety analysis will be performed at the same time. Herein, potential factors of the clinical trial that could negatively impact patient outcomes will be addressed. These factors include adverse effects of ICG administration and factors from the clinical trial process that negatively impact the conventional treatment course of patients. If any concerns are identified on interim safety analysis, the study could temporarily pause enrollment until the issues are addressed. This is to supplement study stopping rules delineated in 9.6 and Data and Safety forms.

The study schedule will be divided into 2 periods: (1) the intra-surgical period which starts at the time of ICG injection and ends when the surgical procedure is terminated and (2) the postoperative period which begins at the end of surgery and ends 30 days postoperatively.

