## Description of Statistical Methods

- - 1. General Approach

Descriptive statistics will be used to summarize patients’ baseline characteristics and baseline disease characteristics. This information will be presented with percentages, means with standard deviations median and range as suitable. Inferential tests will use a null-hypothesis significance testing of <0.05.

- - 1. Analysis of Primary Endpoint(s)

*11.4.2 Primary endpoint – Leak rate*

We will assess the association between ICG perfusion and leaks using a chi-square test. Logistic regression analysis will be further utilized to evaluate covariates influencing the presence/absence of leaks, with specific attention to the predictive value of percent maximum perfusion metrics and time to maximum metrics at the set timepoints in the protocol. Refer to Sections 3.1 for additional information

- - 1. Analysis Of The Secondary Endpoint(S)

*11.4.3.1 Secondary endpoint –*

We will use descriptive statistics to summerize the grade of leasks and ICG metrics.

*11.4.3.2 Secondary endpoint – ICG logistics*

The results of the survey to be applied to surgeons and other OR staff will be summerized using a descriptive statistics.

- - 1. Safety Analyses

Adverse events will be tabulated by the Medical Dictionary for Regulatory Activities (MedDRA Version 21.1) preferred term and system organ class. The severity of the AE will be assessed by National Cancer Institute (NCI) Common Terminology Criteria for Adverse Events (CTCAE) version 5.0. Using the safety analysis set, descriptive statistics will be used to summarize all on-study AEs, grade 3-4 AEs, treatment-related AEs, grade 3-4 treatment-related AEs, SAEs, treatment-related SAEs, and AEs leading to study therapy discontinuation. Grade 3-4 laboratory abnormalities will be summarized using worst grade NCI CTCAE v5.0 criteria.

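### With 50 patients split 25/25, power for a 25-point leak-rate difference is about 47%, not the stated 80%; 80% power needs a difference of about 37 to 38 points

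*Protocol*

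**What the plan says.** The study has one arm of 50 patients: "The study design consists of a single arm intervention group (n=50"), under Description of the Study Design. Patients are classed afterwards as having normal or reduced perfusion of the cut edge, by a cutoff of 60% of maximum ICG uptake, and leak rates are compared between the two classes.

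Section 10.1 (Sample Size Determination) explains that, with no existing data on ICG perfusion in the pancreas, the number was not derived from a hypothesis and a detectable difference is given instead. It takes the perfusion classes to be equal in size ("Anticipating the balanced number between two groups") and then makes the power claim: "our sample size of 50 will have 80% power to detect at least 25% difference in leaks rate between two group". The reference value is a leak rate of 20% in patients whose perfusion is normal. The synopsis, under Statistical Analyses, says the same: "Our projected sample size of 50 will achieve 80% power to detect at least 25% difference in leaks rate between two group".

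The primary test is a chi-square test (Analysis of Primary Endpoint(s)). On the significance level, the General Approach paragraph says: "Inferential tests will use a null-hypothesis significance testing of <0.05". It does not say whether testing is one- or two-sided. The Statistical Hypothesis section gives the expected direction: "hypoperfusion will be associated with increased rates of pancreatic leaks postoperatively".

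**The concern.** Fifty patients in two groups of 25 is a small sample for comparing proportions between 20% and 45%. The standard error of the difference is about 13 points, so a 25-point difference is just under two standard errors. A true effect of that size sits almost on the two-sided 5% critical value, which means power near one half.

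This matters because the detectable difference is the only quantitative support the protocol offers for 50 patients. Those who approve the study, and those who later read its result, are told that a 25-point difference would be found four times in five. If the real chance is about one in two, a non-significant result says much less about the association than the protocol implies. The study is also meant to inform a later trial of improving remnant perfusion.

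**Working it through.** **Inputs**

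- Total n = 50 (Description of the Study Design; section 10.1).
- Equal groups, so 25 and 25 (section 10.1).
- Leak rate with normal perfusion p1 = 0.20 (section 10.1).
- Difference 0.25. A fall of 25 points from 20% is impossible and the hypothesis is an increase, so p2 = 0.45.
- Pearson chi-square test at 0.05 (Description of Statistical Methods). Two-sided is assumed, as the natural reading of a chi-square test; one-sided is shown as well.

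**Attempt to reproduce the stated 80%**

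Power ≈ Φ((|p2 − p1| − z·SE0) / SE1), where

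- pooled p = (0.20 + 0.45)/2 = 0.325
- SE0 = √(0.325 × 0.675 × 2/25) = 0.1325
- SE1 = √(0.20 × 0.80/25 + 0.45 × 0.55/25) = 0.1277

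Power = Φ((0.25 − 1.96 × 0.1325)/0.1277) = Φ(−0.076) = **0.470**.

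Other methods and readings:

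| Method or reading | Power |
| --- | --- |
| Unpooled variance, two-sided 0.05 | 49.9% |
| Arcsine, two-sided 0.05 | 48.4% |
| Exact enumeration, Pearson chi-square | 49.4% |
| Exact enumeration, Yates correction | 36.0% |
| Exact enumeration, Fisher | 36.1% |
| One-sided 0.05, pooled approximation | 59.9% |
| Two-sided alpha 0.20 (not supported by the protocol) | 73.5% |
| All 75 screened patients analysed | 64.2% |
| 25% read as relative (20% v 25%) | 6.2% |
| 20% read as the overall rate (7.5% v 32.5%) | 60.4% |
| 50 patients per group | 76.9% |

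None of these reaches 80%. The closest is 50 per group, for which the difference detectable at 80% power is 26.0 points. A confusion of per-group and total numbers may therefore be the origin of the figure, but that is inference, and the protocol is clear that 50 is the total.

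**Difference detectable with 80% power at 25/25, from 20%**

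Solving the same formula for p2:

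- Two-sided, normal approximation: 37.7 points (20% v about 58%).
- Two-sided, exact Pearson: 36.5 points (20% v about 57%).
- One-sided, normal approximation: 33.2 points.

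**Sample size for 80% power at 20% v 45%**

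n per group = [1.96 × √(2 × 0.325 × 0.675) + 0.8416 × √(0.20 × 0.80 + 0.45 × 0.55)]² / 0.25²
= [(1.96 × 0.6624 + 0.8416 × 0.6384)/0.25]² = 7.342² = 53.9, so 54 per group and **108 in total** (62 per group and 124 in total with continuity correction).

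**Unequal groups**

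The split depends on how many patients fall below the uptake cutoff, and the protocol has no data on this. The splits below are assumptions chosen to show the range (pooled approximation, two-sided 0.05).

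| Normal / reduced | Power at 20% v 45% | Detectable difference at 80% power |
| --- | --- | --- |
| 30 / 20 | 47% | 38 points |
| 35 / 15 | 44% | 40 points |
| 40 / 10 | 38% | 45 points |
| 15 / 35 | 37% | 41 points |
| 10 / 40 | 27% | 47 points |

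Mild imbalance costs almost nothing; marked imbalance costs a good deal, and more when the reduced-perfusion group is the larger. The analysed number may also fall below 50. Cases with failed surgeon blinding are dropped from analysis (Evaluation of Success of Blinding), and patients lacking essential data may be excluded (Handling of Missing Data).

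**The case against.** The best defence is that this is a preliminary study. The synopsis describes the aim as gathering early data on feasibility and association, and section 10.1 says outright that the number was not derived from a hypothesis. The power sentence then only describes a number fixed on other grounds, and correcting it need not change the design. That is right, and it is why no increase in sample size is asked for. It does not make the sentence true: a preliminary study may have low power, but it should not report 80% when it has 47%.

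A second point is that sidedness is not stated, and the 37 to 38 points rest on two-sided testing. One-sided testing lowers the detectable difference to about 33 points and raises power at 25 points to about 60%. It narrows the gap without closing it.

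Third, equal groups are disclosed as an assumption, so possible imbalance is not a separate error. That is fair. The unequal splits above are illustrations, and the finding stands at 25/25 without them.

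Finally, how a future reader would take a null result cannot be known. What can be said is that a true 25-point difference would be missed about half the time.

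**Conclusion.** The stated power is wrong in section 10.1 and in the synopsis. On the protocol's own inputs, power for 20% against 45% is 47% (49% exact), some 30 points below the claim. The difference detectable with 80% power is 37.7 points (36.5 exact) instead of 25. The sample that would support the claim is 108, more than twice the planned 50.

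The conclusion assumes 25 patients per group, all 50 analysed, a Pearson chi-square test and two-sided alpha of 0.05. Only sidedness is not fixed by the protocol, and changing it does not rescue the figure. The sentence must be corrected, because it is the protocol's only numerical justification of its size.

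**What to change.** Keep 50 patients and replace the power sentence in section 10.1 and in the synopsis with wording such as:

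> With 50 evaluable patients divided equally between normal and reduced perfusion, a chi-square test at two-sided 0.05 has 80% power for a difference of about 38 percentage points (20% v 58%) and 47% power for a difference of 25 points. Power will be lower if the groups are markedly unequal or fewer than 50 patients can be analysed.

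State the sidedness of the test, write the difference in percentage points, and describe the comparison as preliminary, in line with the stated aim. Reporting the leak-rate difference with its 95% confidence interval as the main result would suit such a study; that is a recommendation and not part of the correction.

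The cost is a wording change in two places and a less favourable stated figure, with no extra patients and no change to procedures. If the sponsor instead wants 80% power for a 25-point difference, the sample would have to be about 108 evaluable patients in equal groups, which is a different study.
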